### Interventions

#### Treatment Schedule and Adherence Monitoring

All participants will undergo one session per week for 6 weeks (6 sessions in total). Treatment adherence will be monitored throughout the intervention period using attendance records completed by the treating therapist. Participants will be required to attend at least 80% (5/6) of the scheduled in-person treatment sessions to be considered adherent to the protocol and eligible for inclusion in the per-protocol analysis.

#### EDN Plus Therapeutic Exercise Group

Participants allocated to the experimental group will receive 6 weekly treatment sessions of approximately 60 minutes each. Each session will consist of 30 minutes of ultrasound-guided EDN followed immediately by 30 minutes of cervical-specific therapeutic exercise.

Active MTrPs will be identified by trained physiotherapists using standardized diagnostic criteria based on current expert consensus. An active MTrP will be defined as the presence of: (1) a palpable taut band within the muscle, (2) a hypersensitive spot within the taut band, and (3) reproduction of the participant’s familiar neck pain during manual compression. When present, local twitch responses and referred pain patterns will also be recorded. Prior to participant recruitment, all treating physiotherapists will undergo calibration training sessions to standardize MTrP identification procedures [31,32].

The muscles eligible for treatment include the occipitofrontalis, sternocleidomastoid, splenius capitis, anterior, middle, and posterior scalenes, upper, middle, and lower trapezius, and multifidus at the C6 level [33]. However, only muscles demonstrating active MTrPs during clinical examination will be treated. A maximum of 6 active MTrPs will be treated per session, using 1 sterile disposable needle per trigger point.

Participants will be positioned according to the muscle being treated, and the skin will be disinfected with chlorhexidine prior to needle insertion. Sterile 0.25×25 mm acupuncture needles will be inserted under real-time ultrasound guidance to ensure accurate needle placement and patient safety. Needle depth will be individualized according to the target muscle and participant anthropometric characteristics.

Following needle insertion, electrical stimulation will be applied using a TensMed S82 (Enraf-Nonius). The stimulation parameters will be standardized at a frequency of 8 Hz and a pulse duration of 250 μs, delivered through asymmetrical biphasic square-wave currents for 30 minutes [34]. Electrical intensity will be progressively increased until participants report a strong but comfortable sensory response without pain or intolerance. The final intensity (mA) delivered during each session will be recorded.

To minimize treatment variability, all therapists will follow a standardized intervention manual detailing patient positioning, trigger point identification, needle placement procedures, stimulation parameters, and safety precautions [31,32,35]. A treatment record form will be completed after each session documenting the muscles treated, number of needles inserted, stimulation intensity, treatment duration, and any adverse events.

Participants will be informed about the possibility of postneedling soreness and will be instructed to apply local cryotherapy if required during the first 48 hours. A follow-up telephone call will be conducted 48 hours after each treatment session to monitor adverse events and ensure participant safety.

Immediately after EDN, participants will perform the same cervical-specific therapeutic exercise program received by the control group. Therefore, this trial is designed to evaluate the added value of incorporating EDN into an exercise-based physiotherapy program rather than isolating the specific physiological effects of EDN itself.

#### Therapeutic Exercise Group

Participants in the therapeutic exercise group will undergo a 6-week progressive exercise program targeting the cervical flexor and extensor muscles, with 1 session per week (6 sessions in total). The program is designed to enhance activation, recruitment, and endurance of the deep cervical flexors and extensors, improve muscle cocontraction and spinal stability, and promote neuromuscular control of the cervical spine [36,37].

Exercises are progressive, with each week incorporating the exercises from previous weeks, as detailed in Table 1, which specifies the sets, repetitions, contraction duration, and rest intervals. This structured progression aims to optimize muscle strength, endurance, and functional recovery, contributing to pain reduction and improved cervical function.

**Table 1. T1:** Cervical spine specific exercise program.

Week, phase, and exercise	Description	Repetitions/sets	Benefit
Week 1, phase 1: activation of deep cervical flexors			
Cranio-cervical flexion (supine)	Supine with towel under neck. Slowly nod the head, activating the deep flexors without moving the larger muscles.	3×10, 10 s hold, 10 s rest	Activates deep cervical flexors, improves neck stability and posture
Cranio-cervical flexion (sitting)	Seated, feet on the floor, hips and knees at 90°. Perform slow head nods.	3×10, 10 s hold, 10 s rest	Strengthens deep flexors, improves postural control
Cervical side bending (sitting)	Tilt the head slowly to each side while keeping the shoulders relaxed.	3×10 per side, 10 s hold, 10 s rest	Improves lateral neck strength, reduces asymmetry
Scapular retraction + cranio-cervical nod	Seated or supine, gently squeeze the shoulder blades while nodding the head.	3×10, 10 s hold	Activates deep flexors and scapular stabilizers, improves posture
Chin tuck with resistance band	Supine or standing, band around forehead. Perform slow chin tucks against gentle resistance.	3×10, 10 s hold	Strengthens deep flexors, improves head alignment
Week 2, phase 2: isometric cocontraction			
Deep and superficial flexors (supine)	Physiotherapist resists cranio-cervical flexion.	10 repetitions × 10 s hold, 10 s rest	Improves cocontraction and neck stability
Flexors + rotators + lateral muscles (supine)	Flex the neck while therapist resists rotation and side bending.	10 repetitions per side × 10 s hold	Enhances multimuscle activation and motor control
Isometric cervical extension	Seated, push the head backward into the therapist’s hand without moving.	10×10 s hold	Strengthens deep extensors, reduces flexion dominance
Isometric side bending	Seated, push the head laterally against hand resistance.	10×10 s per side	Improves lateral neck endurance and symmetry
Week 3, phase 3: eccentric/isokinetic^a^			
Eccentric extensors (seated)	Extend the neck, then slowly flex to full flexion.	10 repetitions	Improves extensor control, strength, and mobility
Eccentric flexors (quadruped)	Flex the neck slowly from neutral, then extend fully.	10 repetitions	Improves flexor control, range of motion, and motor coordination
Isokinetic extensors (quadruped + resistance band)	Band around the head, perform cervical extension, then slowly flex.	10 repetitions	Enhances dynamic extensor strength and neck stability
Prone Y, T, W lifts	Prone on a table, lift the arms in Y, T, and W positions while keeping the neck neutral.	3×10	Strengthens scapular and cervical extensors, improves posture
Quadruped “cat-cow” with cranio-cervical focus	Move through flexion and extension while maintaining controlled cranio-cervical movement.	3×10, slow and controlled	Improves cervical and spinal mobility, promotes neuromuscular coordination between the cervical and thoracic spine, and reinforces controlled craniocervical movement

a The exercises and parameters from week 3 (phase 3: eccentric/isokinetic) were repeated during weeks 4 to 6 to complete the 6-week intervention period.

Therefore, this trial should be interpreted as a pragmatic effectiveness study evaluating the added value of EDN when incorporated into an exercise-based physiotherapy program rather than a mechanistic study designed to isolate the specific physiological effects of EDN.

### Data Collection and Outcome Measures

At the start of the study, demographic and clinical data will be collected, and all outcome measures will be assessed at 3 time points: baseline (preintervention), immediate posttreatment (1 d after the last session), and short-term follow-up (2 mo postintervention). Outcome assessments will be performed by a blinded evaluator using standardized procedures and calibrated instruments to improve measurement reliability and reproducibility.

The primary outcome is the Neck Disability Index (NDI), a 10-item questionnaire assessing activities of daily living. Each item is scored on a 0‐5 Likert scale. Total scores are converted to percentages (0%‐100%), with 0% indicating full independence and 100% indicating complete dependence [38,39].

Secondary outcome measures include the following:

Visual Analog Scale: Used to assess pain intensity, participants will mark their pain level on a 100-mm horizontal line, with 0 mm representing “no pain” and 100 mm representing the “worst imaginable pain” [40].McGill Pain Questionnaire: A self-administered multidimensional measure of pain widely used across different patient populations, assessing both the quality and intensity of pain. It includes 3 components: sensory-discriminative, cognitive-evaluative, and affective-motivational [41].SF-36 (Short Form-36 Health Survey) Questionnaire: Used to assess quality of life, the SF-36 consists of 36 items across 8 subscales: physical functioning, role physical, bodily pain, general health, vitality, social functioning, role emotional, and mental health. Scores range from 0% to 100%, with higher scores indicating better perceived quality of life [42].Tampa Scale for Kinesiophobia: A 17-item questionnaire measuring fear of movement and (re)injury. It uses a 4-point Likert scale ranging from “strongly disagree” to “strongly agree” [43].Cervical range of motion: Measured using a digital goniometer (Pro Motion Capture, Werium). Participants will sit comfortably in a chair with feet flat on the floor, hips and knees at 90°, and buttocks supported against the backrest [44].Pressure algometry at MTrPs: A Wagner FPI 10 algometer with a rubber tip and dial will measure pressure applied to MTrPs in 0.5 kg increments. Evaluated muscles include the occipitofrontalis, splenius capitis, sternocleidomastoid, anterior, middle, and posterior scalenes, upper, middle, and lower trapezius, supraspinatus, infraspinatus, and multifidus at C6 [45].Pittsburgh Sleep Quality Index: Measures sleep quality and consists of 24 items, of which 19 are self-administered and 5 are for cohabitants. Items are grouped into 7 components: subjective sleep quality, sleep latency, sleep duration, habitual sleep efficiency, sleep disturbances, use of sleep medication, and daytime dysfunction. A 4-point Likert scale (0=“rarely,” 1=“sometimes,” 2=“often,” 3=“almost always”) is used, with items 2 and 5 reverse scored. Total scores range from 0 to 21, with higher scores indicating more severe sleep problems [45].Pain Catastrophizing Scale (PCS): A self-administered questionnaire assessing pain catastrophizing in clinical and nonclinical populations. Catastrophizing is defined as an exaggerated negative orientation toward noxious stimuli and influences pain perception and coping. The PCS consists of 13 items evaluating rumination, magnification, and helplessness, scored on a 5-point scale [46].Cervical isometric strength test: Maximum isometric strength of the neck extensors will be measured using a handheld dynamometer. Participants will sit with their feet flat on the floor, hips and knees at 90°, and neck in a neutral position. The handheld dynamometer will be held against the occiput with both hands, and participants will resist cervical extension isometrically for 3 seconds until maximum force is achieved [47].Cervical flexor endurance test: To assess maximal isometric strength of cervical flexors, participants will lie supine performing a double chin tuck and maintain this position. They will lift their head approximately 2.5 cm off the table and hold for as long as possible, while the evaluator measures endurance time. The test will end if the participant loses the position for more than 1 second or requests to stop due to pain or fatigue [48].

These outcome measures provide a comprehensive assessment of pain, disability, psychological factors, quality of life, and cervical muscle performance, allowing evaluation of both the immediate and short-term effects of the interventions.

### Sample Size Calculation

The sample size was calculated for the primary outcome, the NDI, based on detecting a clinically meaningful between-group difference of 7.5 points, which is consistent with previous studies on the responsiveness of the NDI. Assuming a standard deviation of 10.58 points, a 2-sided significance level of .05, and 80% statistical power, the required sample size was 32 participants per group. To account for an anticipated 10% (3/32) loss to follow-up, the final target sample size was increased to 35 participants per group, resulting in a total sample of 70 participants.

### Randomization

Participants will be randomly assigned to either the experimental group (EDN plus therapeutic exercise) or the control group (therapeutic exercise alone) using a computer-generated randomization sequence created by an independent statistician.

Allocation concealment will be ensured using sequentially numbered, opaque, sealed, tamper-evident envelopes prepared by an independent researcher not involved in participant recruitment, outcome assessment, or treatment administration. Envelopes will be opened sequentially only after completion of the baseline assessment and immediately before the first intervention session.

The outcome assessor will remain blinded to group allocation throughout the trial. Participants and treating physiotherapists cannot be blinded due to the nature of the interventions.

### Data Analysis

Data will be analyzed using SPSS (version 28.0; IBM Corp) and will follow the intention-to-treat principle, whereby all randomized participants will be analyzed in the groups to which they were originally assigned, regardless of treatment adherence or completion. Additionally, a per-protocol analysis will be conducted including participants who complete at least 80% (5/6) of the in-person treatment sessions. All analyses will be conducted by a statistician blinded to group allocation.

Descriptive statistics will be calculated for all variables. Continuous variables will be presented as mean (SD) or median (IQR), depending on the data distribution, while categorical variables will be expressed as frequencies and percentages.

Baseline comparability between groups will be assessed using independent Student *t* tests for normally distributed continuous variables, Mann-Whitney *U* tests for nonnormally distributed variables, and chi-square tests for categorical variables. Normality will be evaluated using the Kolmogorov-Smirnov test and visual inspection of histograms.

A statistically significant group × time interaction will be interpreted as evidence of differential treatment effects over time. To evaluate the effects of the intervention over time and between groups, linear mixed-effects models will be used, including group (experimental vs control), time (baseline, postintervention, and 2-mo follow-up), and the group × time interaction as fixed effects, with participants included as random effects. This approach allows appropriate handling of repeated measures and missing data.

If model assumptions are not met, appropriate nonparametric alternatives (eg, Friedman test for within-group comparisons and Mann-Whitney *U* test for between-group comparisons with adjusted post hoc analyses) will be applied. Adjustment for multiple comparisons among secondary outcomes will be performed using the Holm-Bonferroni procedure.

Missing data will be handled using multiple imputation methods under the assumption of missing at random. Sensitivity analyses will be conducted to assess the robustness of the findings. Dropouts and losses to follow-up will be reported and compared between groups. Twenty imputed datasets will be generated using multiple imputation procedures.

The primary end point will be the between-group difference in change in NDI scores from baseline to postintervention. Postintervention was defined as 1 day after completion of the sixth treatment session. Age, sex, and baseline NDI values will be explored as potential covariates if baseline imbalance is detected. Secondary outcomes will include changes in Visual Analog Scale, McGill Pain Questionnaire, quality of life SF-36, Tampa Scale of Kinesiophobia, cervical range of motion, Pittsburgh Sleep Quality Index, PCS, pressure pain threshold, cervical isometric strength, and cervical flexor endurance. Effect sizes (eg, Cohen *d*) will be calculated to assess the magnitude of differences.

Additionally, the clinical relevance of the findings will be assessed by comparing observed changes with established minimal clinically important differences. Based on previous studies in patients with neck pain, a change of approximately 7.5 points on the NDI and 1.5 points on pain intensity scales has been considered clinically meaningful and will be used to aid the interpretation of clinical relevance [49]. For other secondary outcomes, where established minimal clinically important differences are available, these will be considered to aid the interpretation of clinical significance.

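### The primary endpoint is one contrast (NDI change to postintervention), but the only test given an inferential reading is the three-timepoint group × time interaction, and the fallback is not tied to that contrast either

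*Protocol article*

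**What the plan says.** All of this stands in the protocol article, under Data Analysis unless another section is named.

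- **Endpoint.** "The primary end point will be the between-group difference in change in NDI scores from baseline to postintervention". This is one comparison at one visit, the day after the sixth session.
- **Model.** A linear mixed model with group, "time (baseline, postintervention, and 2-mo follow-up), and the group × time interaction as fixed effects, with participants included as random effects".
- **Reading of the result.** "A statistically significant group × time interaction will be interpreted as evidence of differential treatment effects over time". No other test result is given an interpretation.
- **Baseline.** "Age, sex, and baseline NDI values will be explored as potential covariates if baseline imbalance is detected". Adjustment for baseline NDI therefore depends on the observed data.
- **Fallback.** If assumptions fail, the examples are the "Friedman test for within-group comparisons" and the Mann-Whitney "test for between-group comparisons with adjusted post hoc analyses". The score to which Mann-Whitney is applied is not stated.
- **Sample size (Sample Size Calculation).** Based on "detecting a clinically meaningful between-group difference of 7.5 points", with SD 10.58, two-sided alpha .05 and 80% power, giving 32 per group before loss to follow-up.

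**The concern.** The endpoint and the sample size concern one difference at one visit. The interaction asks a different question: whether the arms differ in change at postintervention, at 2 months, or at both. A significant result does not say which visit produced it, and a non-significant result can hide a real effect at postintervention that has waned by 2 months. If the conclusion is drawn from this test, it may not be about the declared primary endpoint, and its power is not the stated 80%.

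The fallback has a similar gap. A Friedman test within an arm compares that arm with itself over time and cannot speak to EDN plus exercise against exercise alone. The Mann-Whitney test is between groups, but the text does not say that it is applied to the baseline-to-postintervention change. The switch depends on what the data look like, so what it switches to should be fixed beforehand.

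**Working it through.** **Inputs.** From the protocol: difference 7.5, SD 10.58, two-sided alpha .05, power 80%, 32 per arm, three visits, two arms. Assumed, because the protocol gives none: the correlations between NDI scores at the three visits.

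**1. The plan's own figure.** n = 2(z₀.₉₇₅ + z₀.₈₀)² × SD² / difference² = 2 × (1.960 + 0.842)² × 10.58² / 7.5² = 31.2, so 32 per arm. It reproduces, and it is the formula for a single two-group comparison.

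**2. Degrees of freedom.** (2 − 1) × (3 − 1) = 2 for the interaction, against 1 for the declared contrast. The 5% critical chi-square values are 5.99 and 3.84.

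**3. Power of the declared contrast.** With a baseline-to-postintervention correlation of 0.5, the variance of change is 2(1 − 0.5) × 10.58² = 10.58², so it does not matter here whether 10.58 is the SD of scores or of changes. The noncentrality is λ₁ = 7.5² / (2 × 10.58² / 32) = 56.25 / 6.996 = 8.04, which gives 81% power. With no effect at postintervention the rejection rate is 5%.

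**4. Power of the interaction.** Let a and b be the effects at postintervention and at 2 months in units of 7.5 points. Let v be the variance of change at 2 months and c the covariance of the two changes, both in units of 10.58². Then λ₂ = 8.04 × (v·a² − 2c·ab + b²) / (v − c²).

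Correlations are listed as baseline–post, baseline–2 months, post–2 months.

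| Assumed correlations | v, c | 2 months only (a=0, b=1) | Half kept (a=1, b=0.5) | Sustained (a=1, b=1) |
|---|---|---|---|---|
| 0.5, 0.5, 0.5 | 1, 0.5 | λ₂ 10.72, 84% | λ₂ 8.04, 72% | λ₂ 10.72, 84% |
| 0.5, 0.5, 0.7 | 1, 0.7 | λ₂ 15.77, 95% | λ₂ 8.67, 75% | λ₂ 9.46, 79% |
| 0.5, 0.4, 0.6 | 1.2, 0.7 | λ₂ 11.32, 86% | λ₂ 8.49, 74% | λ₂ 9.06, 77% |
| Declared contrast | – | 5% | 81% | 81% |

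Example, first row, half kept: 8.04 × (1 − 0.5 + 0.25) / 0.75 = 8.04. The noncentrality equals that of the single contrast but is judged against 5.99 instead of 3.84.

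**5. Small-sample check.** The first row matches the random-participant model that the protocol describes. With a noncentral F distribution and residual df 2 × (64 − 2) = 124, the contrast has 80.3% power. The interaction has 83.4% (2 months only), 70.9% (half kept) and 83.4% (sustained). For 80% power in the half-kept case the interaction needs 40 per arm.

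**6. Sensitivity to the SD.** The protocol does not say whether 10.58 is the SD of scores or of changes. If it is the SD of scores, with one common correlation of 0.3 to 0.7, power is 66.2% to 95.3% for the contrast and 55.3% to 91.0% for the interaction when half the effect is kept. With an effect only at 2 months, the interaction is significant in 68.6% to 97.0% of trials. The levels move, but the gap between the two tests remains.

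**The case against.** The strongest reply is that the planned model already yields the endpoint. With baseline as the reference visit, one of the two interaction coefficients is exactly the between-group difference in NDI change to postintervention. The sentence about the interaction is a general remark on interpretation, it is true as written, and the protocol states no formal success criterion. The exact contrast might be named in an analysis plan that is not shown. The first part stands: a reader might infer that the planned tests do not address the endpoint at all, and that would be wrong. But the article does state how the model's result will be read, and it attaches that reading to the omnibus test. This is a mismatch in what is written, not a missing detail.

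On size, the case of an effect at 2 months only is extreme, and nothing in the protocol makes it likely. A reader might infer a general loss of power, but a sustained effect gives 77–84% against 81%. The loss depends on how the effect behaves after treatment ends.

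On the fallback, three stronger readings fail:

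- That it abandons intention to treat. The same section commits to analysing all randomized participants as assigned and to multiple imputation with 20 datasets, so a Friedman test need not drop anyone.
- That Mann-Whitney ignores baseline or wastes a fixed share of the sample. The text does not say whether it uses postintervention scores or changes, so no efficiency loss can be computed. Applied to the change, it would be a between-group test of the endpoint.
- That Friedman is the efficacy test. The text assigns it to within-group comparisons, and both tests are given only as examples.

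**Conclusion.** The concern holds in this form: the declared endpoint and the sample size call for one 1-df contrast, while the only test with a stated inferential reading is a 2-df interaction that also draws on the 2-month visit. Used as written, it can give a positive reading when the primary contrast is null (84–95% of trials against 5%, for 7.5 points at 2 months only), and it can miss a real primary effect more often than planned (72–75% power against 81%, when half of 7.5 points is kept). It costs little or nothing when the effect is sustained (77–84% against 81%). These figures rest on 32 per arm, SD 10.58, large-sample power and assumed correlations of 0.4 to 0.7. The mismatch itself needs no assumption. The fallback adds a smaller fault of the same kind, since its between-group test is not tied to the declared change.

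**What to change.** - **Primary test.** State that it is the single model contrast, EDN plus exercise minus exercise alone, for NDI at postintervention, adjusted for baseline NDI in every case and not only when imbalance is seen. Report the estimate and 95% CI at two-sided alpha 0.05. In practice, either keep baseline as a visit and constrain the arm means to be equal there, or remove it from the outcome and enter it as a covariate.
- **Other NDI results.** Make the omnibus interaction supportive and the 2-month contrast secondary.
- **Fallback.** If assumptions fail, keep the same between-group contrast with bootstrap or robust standard errors. A rank test of the baseline-to-postintervention change can serve as a sensitivity analysis. Do not use within-group tests as evidence of efficacy.
- **Cost.** A few sentences, with no new data or participants. If 10.58 is the SD of change, the sample size calculation already fits the contrast.
- **Timing.** Safety Considerations says that analyses will not be altered once the first participant is registered. The change should therefore be a dated clarification that aligns the test with the endpoint already declared, made before unblinding.

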## Methods

### Study Design

The present clinical trial is justified, with the primary objective of comparing the effectiveness of EDN combined with therapeutic exercise versus therapeutic exercise alone in patients with CNSNP, evaluating its impact on disability, pain, strength, cervical range of motion, quality of life, and sleep.

This study will be conducted as a randomized, controlled, parallel-group, single-blind clinical trial (assessor-blinded), with two intervention arms: (1) EDN combined with therapeutic exercise and (2) therapeutic exercise alone in patients with CNSNP. Participants will be randomly assigned to 1 of the 2 groups in a 1:1 ratio.

This protocol has been developed in accordance with the SPIRIT (Standard Protocol Items: Recommendations for Interventional Trials) guidelines (Checklist 1). The study will be conducted at the Clinical Unit of the Faculty of Health Sciences, University of Almería, Spain. A SPIRIT flow diagram and a structured schedule of enrollment, interventions, and assessments have been included to improve methodological transparency and reproducibility.

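### The mixed model names only a participant random effect; read as a random intercept, it ties the standard error of the primary NDI contrast to all three visit pairs, so type I error is 5% only under a condition the documents do not support (about 3% to about 8% under assumed correlations)

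*Protocol article*

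**What the plan says.** The Data Analysis section of the protocol article puts all three visits into one linear mixed-effects model. The fixed effects are group, "time (baseline, postintervention, and 2-mo follow-up), and the group × time interaction as fixed effects", and the covariance part reads "with participants included as random effects. This approach allows appropriate handling of repeated measures and missing data". The article names no residual covariance structure, random slope or robust variance.

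The same section makes one contrast primary: "The primary end point will be the between-group difference in change in NDI scores from baseline to postintervention". Under Data Collection and Outcome Measures the visits are "baseline (preintervention), immediate posttreatment (1 d after the last session), and short-term follow-up (2 mo postintervention". The 2-month visit is therefore not part of the primary contrast but is part of the model that supplies its standard error.

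If model assumptions fail, the article turns to nonparametric tests. It also promises sensitivity analyses without saying what they are.

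**The concern.** With one score per participant per visit and visit as a category, a participant random effect is ordinarily a random intercept. That is compound symmetry: equal variances, and one correlation shared by baseline-postintervention, baseline-2 months and postintervention-2 months. The model then has a single variance for any change between two visits, estimated from all three pairs.

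The visits are not interchangeable. One precedes treatment, one falls a day after the last session and one comes two months later. Two departures are plausible and push in opposite directions. The two post-treatment scores may agree more with each other than with baseline, which makes the pooled standard error too small for the primary contrast. Or correlation may fall with elapsed time, which makes it too large. With complete data the point estimate is unaffected. What is at stake is the p value and confidence interval of the only primary contrast. The article's statement that the approach handles repeated measures appropriately depends on the covariance being right for that contrast.

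**Working it through.** **Inputs from the article.** Three visits and one primary contrast, as quoted above; "Participants will be randomly assigned to 1 of the 2 groups in a 1:1 ratio"; "detecting a clinically meaningful between-group difference of 7.5 points"; "Assuming a standard deviation of 10.58 points"; "a 2-sided significance level of .05, and 80% statistical power".

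**The plan's own figure.** n per arm = 2 × (1.960 + 0.842)² × 10.58² / 7.5² = 2 × 7.851 × 111.94 / 56.25 ≈ 31.2, rounded up to 32 (a t-based calculation gives 32.2). The stated 32 is reproduced. That calculation uses no visit correlation, so it neither informs this point nor is affected by it.

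**Assumptions.** The documents give no visit-to-visit correlations and no SD by visit. All correlations below are assumed, in the order baseline-post / baseline-2 months / post-2 months. SDs are equal unless stated.

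**Formulas.**
- True variance of a change between visits i and j: V(i,j) = s(i)² + s(j)² − 2 r(i,j) s(i) s(j).
- Variance used by a balanced random-intercept model for any change: the mean of the three V(i,j).
- SE ratio (model/true) for the primary contrast: √(mean V / V(base,post)).
- Large-sample type I error: 2 × [1 − Φ(1.96 × SE ratio)].

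**Results.** Variances are in units of σ². The simulated column is from 100,000 complete-data trials per scenario at 35 per arm.

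| Correlations | Three V | Mean V | SE ratio | Formula | Simulated |
|---|---|---|---|---|---|
| 0.6/0.6/0.6 | 0.80, 0.80, 0.80 | 0.80 | 1.00 | 5.0% | 4.9% |
| 0.7/0.49/0.7 (decay) | 0.60, 1.02, 0.60 | 0.74 | 1.11 | 3.0% | 3.0% |
| 0.7/0.5/0.6 | 0.60, 1.00, 0.80 | 0.80 | 1.15 | 2.4% | 2.4% |
| 0.6/0.4/0.7 (mixed) | 0.80, 1.20, 0.60 | 0.87 | 1.04 | 4.1% | not run |
| 0.5/0.4/0.7 (mixed) | 1.00, 1.20, 0.60 | 0.93 | 0.97 | 5.8% | 5.8% |
| 0.5/0.5/0.7 | 1.00, 1.00, 0.60 | 0.87 | 0.93 | 6.8% | 6.9% |
| 0.5/0.5/0.8 (strong) | 1.00, 1.00, 0.40 | 0.80 | 0.89 | 8.0% | 8.0% |
| 0.4/0.4/0.8 (strong) | 1.20, 1.20, 0.40 | 0.93 | 0.88 | 8.4% | 8.3% |

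**Unequal SDs.** With SDs 9/10.58/12 and correlations 0.6/0.4/0.7, the V are 78.7, 138.6 and 78.2, with mean 98.5. The SE ratio is √(98.5/78.7) = 1.12 and the type I error about 2.8%.

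**Dropout.** With 10% completely random dropout and REML random-intercept fits (20,000 per scenario, 35 per arm), the error was 4.7% for 0.6/0.6/0.6, 3.0% for 0.7/0.5/0.7, 6.9% for 0.5/0.5/0.7, 8.3% for 0.4/0.4/0.8 and 9.2% for the more extreme 0.4/0.4/0.85. A short run of 4,000 fits had given 7.7% for 0.4/0.4/0.8 and 6.5% for 0.5/0.5/0.8; the latter was not repeated at the larger size.

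**Power on the conservative side.** At 32 per arm and a 7.5-point difference, power was 92.6% against 95.0% under decay, and 87.5% against 91.3% with the unequal SDs.

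**After the fix.** A standard error from the baseline-to-postintervention change itself gave 4.9% to 5.1% in every scenario simulated. With complete data and this saturated set of fixed effects, that is the same test as the contrast from an unstructured covariance.

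**The case against.** The strongest reply is that the article does not say random intercept only, compound symmetry or independent residuals. Software such as SPSS sets the random effects and the residual covariance separately, and a full analysis plan that is not shown could add a residual structure. If it does, the point is resolved. What remains is that the article does more than stay silent: it names a covariance term and says the approach is appropriate on that basis.

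The second reply is that both size and direction rest on assumed correlations. That stands. When the two departures act together they partly cancel, and the error is then about 4% to 6%. A reader might infer that the primary p value and interval are simply wrong, or that the trial runs at 8% error. The documents support neither: the error is nominal when SDs and correlations are equal, and about 8% needs a strong pattern. Nor is planned power lost, since the conservative examples stay above the planned 80%.

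Third, the planned multiple imputation with 20 datasets was not simulated, and the unstructured model was checked only through its complete-data equivalent. That limits the exact figures under missing data, not the mechanism.

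Finally, the nonparametric fallback and the sensitivity analyses offer some protection. A Mann-Whitney comparison would not use a pooled visit covariance. But it replaces the model rather than repairing it, and neither provision is tied to the covariance.

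**Conclusion.** The point holds conditionally. If the participant random effect is the only covariance term, the primary contrast has its nominal 5% error only when the average of the three change variances equals that of the baseline-to-postintervention change. Nothing in the article supports that equality, and it cannot be checked from the figures given.

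Under assumed correlations the error is:
- about 3% with decay (standard error about 11% too large, power lower by 2.4 points in that example);
- 4% to 6% in mixed patterns;
- 6% to 7% when the post-treatment visits are moderately more alike;
- about 8% only when they correlate at about 0.8 with each other against 0.4 to 0.5 with baseline.

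Whether this trial's test would be liberal or conservative cannot be said in advance. That uncertainty is the reason not to impose equality. This is a worthwhile and inexpensive improvement, not a fatal flaw.

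**What to change.** In Data Analysis, replace the participant random effect with an unstructured 3×3 within-participant covariance over baseline, postintervention and 2 months. Fit it by REML with Satterthwaite or Kenward-Roger degrees of freedom, and take the baseline-to-postintervention contrast from that model. Name in advance a simpler heterogeneous structure to use if the model does not converge. If the full analysis plan already specifies a suitable structure, state it in the article's terms instead.

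The Safety Considerations section says analyses will not be changed once the first participant is registered. The change should therefore be recorded as a dated amendment, with its reason, before unblinding.

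Cost: six covariance parameters instead of two. At 32 per arm, degrees of freedom for the contrast are about 62 (2 × 31) instead of 124 (2 × 31 × 2), so the critical t is 2.00 instead of 1.98. No new data and no change to the sample size.
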